**Exclusion criteria**
Another sibling participates in the trial.The parent is receiving another video feedback intervention (Video-Feedback Intervention to Promote Positive Parenting (VIPP), Video-Feedback Intervention to Promote Positive Parenting and Sensitive Discipline (VIPP-SD), Marte Meo, Video Parent-Child Interaction, Paediatric Autism Communication Therapy) either remotely or in person.The child lives with the parent <50% of the time or is in a 24-hour residential placement (inpatient unit or residential school).The family is under active family court proceedings.

### Recruitment

#### Identification of Potential Participants for the RCT

During the recruitment stage, potential study participants will be identified through 2 methods: either directly by clinicians during routine clinical contact or via site mail-outs that utilize the service’s referral or waiting or active caseload lists. In both cases, eligible participants will receive a summary of the study. For cases referred by a participant identification center, clinicians will receive guidance information. Additionally, participant identification centers will be provided with supporting information about the study in case they wish to refer a parent of a suitable child.

Interested parents who receive the study information will contact the researcher directly. The researcher will respond to all expressions of interest via email or SMS text message, offering to discuss the study in more detail. If the potential participant does not respond after 3 attempts, no further contact will be made. For those who do respond, a time will be scheduled to discuss the study and review the participant information sheet (PIS).

#### Identification of Process Evaluation Interview Participants

The study will use random sampling to identify potential interview participants from among the parents who consented and were deemed eligible for the trial. We will ensure a balanced sample across variables such as group allocation and site. Clinical service staff who have provided VIG to at least one family will be approached for an interview, with a minimum of 1 practitioner recruited per site. Additionally, all service managers will be invited to participate in an interview.

### Consent

Before any data collection, including screening, written informed consent will be obtained from all study participants through an online form via Qualtrics (Qualtrics International Inc.). Participants will first receive the PIS when they express interest in the study. They will then discuss the PIS with a researcher to ensure full understanding. The PIS includes information about the intervention, the research tasks required, the randomization process, details of ethical approval, and how any data will be managed and stored. All personal information will be stored securely within the study host organization, and anonymized data will be transferred from clinical staff involved in VIG delivery or collaborating organizations. At the end of the meeting, participants will receive a personalized link to the informed consent form via email. The consent form was designed in accordance with the joint statement on e-consent from the Health Research Authority and the Medicines and Healthcare Regulatory Agency [51]. If participants are unable to complete the consent process in Qualtrics, an editable offline version of the consent form will be provided, which they can sign by hand and return to the research team.

Consenting and eligible participants will receive a child notification letter that explains the purpose and process of the study to the children. This letter will include information on how children can contact the trial manager if they wish to do so.

For participants in the process evaluation interviews, which include both clinical service staff and parents, a separate consent form will be obtained alongside a PIS.

### Screening of Potential Participants for RCT Eligibility

The screening assessment will be conducted over the phone or via videoconference by a researcher using a standardized form. The Vineland Adaptive Behavior Scales (Vineland-3; 52) will be completed during the same meeting or in a subsequent appointment if necessary. Once screening is complete and eligibility is confirmed, participants will receive a personalized link to the first data collection questionnaire (baseline).

### Randomization

Randomization will occur after participants have provided consent, had their eligibility confirmed through the screening process, and completed baseline data collection. Participants will be randomly assigned on a 1:1 basis to 1 of the 2 study arms (VIG + TAU vs TAU). Random block allocation stratification techniques will be used to ensure a balanced sample across variables such as group allocation and site.

### Sample Size and Power

As this study is a feasibility RCT, a power calculation was not used to estimate the target sample size. Instead, we examined similar studies [44,52] to determine an appropriate recruitment rate for the study. Based on this analysis, we expect to recruit at least 50 participants from approximately 100 families invited to participate. The feasibility of recruitment will be assessed using a hypothesis-testing approach [53]. This assessment is 1 of the 3 primary research objectives, with a green signal indicating a recruitment rate of 50% of eligible families, amber indicating a rate of 35%-50%, and red indicating less than 35%. To achieve 90% power and a 5% 1-sided α, 97 families will need to be approached.

### Intervention

#### Video Interaction Guidance

The VIG intervention involves the practitioner capturing a short video of the parent interacting with their child during the first meeting, which lasts approximately 20 minutes. In the subsequent meeting, known as the shared review, the practitioner and parent watch selected moments from the video where the interaction between parent and child is particularly positive, based on the parent’s successful communication [30]. The practitioner guides the parent in identifying these moments and highlights their contributions to successful, attuned interactions.

The VIG practitioner facilitates the video recording of a parent-child interaction during an initial meeting with the parent before the recording date. In this meeting, the parent identifies their goals for the VIG intervention. The practitioner assists the parent in recognizing when these goals are being met, even if only briefly, and they discuss activities where such moments might occur. The parent is encouraged to engage in 1 of these activities during the recorded interaction with their child. This approach ensures that the video captures a particularly positive interaction, rather than just typical free play. The chosen activity should be enjoyable and comfortable for both the parent and child. Typically, VIG practitioners film for 5-10 minutes.

For this study, remote meetings are conducted via familiar video calling platforms such as Microsoft Teams (Microsoft Corporation) or Zoom (Zoom Video Communications, Inc.); however, the initial meeting may occur face-to-face if both the practitioner and parent agree. The practitioner helps the parent and child set up the activity, ensuring good visibility and audio. Afterward, they start the recording and turn off their own camera and microphone. They monitor the recording, intervening if the child or parent becomes upset, with the goal of maintaining a positive interaction. Afterward, the practitioner analyzes the recording using principles of attuned interaction, identifying short clips of the most attuned moments for review with the parent. Shared review meetings typically last between 30 minutes and 1 hour. Each recording and review session constitutes 1 cycle of VIG intervention, with 3-5 cycles making up a full intervention. Typically, 3 cycles are offered, with the option to request 2 additional cycles. For the purposes of this study, the maximum intervention duration is 12 weeks, which includes an introductory meeting and a review session. Parents in the VIG group may also receive additional support, either face-to-face or remotely, as provided by their service.

#### Treatment as Usual

Participants allocated to TAU will serve as the comparison group and receive the standard clinical care provided by the specialist mental health service. In parallel with the feasibility RCT, a survey of specialist mental health services across the United Kingdom will be conducted to provide an in-depth description of how widely these services offer video feedback and other interventions, at either the referral/waiting list stage or the active caseload phase.

#### Primary Outcomes

##### Summary

The primary outcomes being assessed include the feasibility of delivering and evaluating remote VIG, the participant recruitment rate, study retention at the 6-month follow-up, and the VIG completion rate. The primary outcomes that will be analyzed are described in the subsequent sections.

##### Recruitment

The study will record the number of referrals directly from clinicians, the number of individuals on mailing lists who were emailed study information, the number of interested parents undergoing screening, the number deemed eligible or ineligible (with reasons for ineligibility), the number who provide consent, the number randomized, and the reasons for refusing randomization. The recruitment rate will be estimated based on the number of parents found eligible for the trial after formal screening and the number of those eligible who are randomized. The desired criterion is that at least 50% of eligible parents are randomized. However, the traffic light system sets 35% as the threshold for the amber zone, meaning 34 out of 97 eligible parents would need to be randomized. If recruitment falls within the amber zone but exceeds the critical value of 42 (54%), minor adjustments will be needed to improve recruitment. If recruitment falls below 42, major changes will be necessary.

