## Methods

### Study Design

This feasibility RCT will involve 50 parents, who will be allocated on a 1:1 basis to either the intervention or treatment as usual (TAU), along with an embedded process evaluation. Additionally, service use data will be collected for cost comparison as part of a parallel feasibility economic evaluation (Figure 1).

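### The amber zone for recruitment is split by a fixed count of 42, which suits only about 94 to 98 eligible parents, leaves 42 itself unassigned and is printed with a wrong percentage

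*Protocol article*

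**What the plan says.** All references are to the protocol article.

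- **Study Design:** "This feasibility RCT will involve 50 parents", allocated 1:1.
- **Sample Size and Power:** recruitment feasibility is judged by a hypothesis test. Green is 50% of eligible families, amber 35% to 50%, red below 35%. "To achieve 90% power and a 5% 1-sided α, 97 families will need to be approached".
- **Table 1:** green is at least 50% of eligible parents, illustrated as 50 of 97 eligible; red is fewer than 35%.
- **Primary Outcomes, Recruitment:** the rate is the number randomized over the number found eligible after formal screening. "The desired criterion is that at least 50% of eligible parents are randomized". For the lower limit, "the traffic light system sets 35% as the threshold for the amber zone, meaning 34 out of 97 eligible parents would need to be randomized". Inside amber, a result that exceeds a critical value of 42, printed with 54% in brackets, calls for minor adjustments. The next sentence reads: "If recruitment falls below 42, major changes will be necessary".

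**The concern.** The outcome is a rate, and its green and red limits are rates that can be applied to any number of eligible parents. The line inside amber is the only limit given as a bare count. It was worked out for a planned denominator of 97, but the denominator used in the analysis is whatever screening yields. The article gives no rule for another denominator, and the one percentage that could have served as a scalable version does not match the count.

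The wording also covers results above 42 and below 42, but not 42.

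At stake is the grading of an amber result on one of three primary feasibility outcomes. Followed as written, the rule can grade recruitment as needing major changes when the plan's own test is passed, or minor adjustments when it is not.

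**Working it through.** **Inputs.** Null rate 35% (red/amber limit), alternative 50% (green limit), one-sided alpha 5%, power 90%, n = 97, critical count 42, target 50 randomized. All are from the sections cited above.

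**1. Reproduce n = 97.** One-sample proportion, normal approximation:

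n = [(1.645·√(0.35·0.65) + 1.282·√(0.5·0.5)) / 0.15]² = [(0.7845 + 0.6408) / 0.15]² = 90.3.

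With continuity correction: (90.29/4)·[1 + √(1 + 2/(90.29·0.15))]² = 96.84, rounded up to 97. The planned number is sound.

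**2. Reproduce 42.** 97·0.35 + 1.645·√(97·0.35·0.65) = 33.95 + 7.73 = 41.7, or 42.2 with continuity correction. So 42 belongs to n = 97.

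**3. The printed percentage.** 42/97 = 43.3%, whereas 54% of 97 is 52.4. Since 54% is above the 50% green limit, it cannot divide amber.

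**4. The unassigned value.** Exact binomial at n = 97:

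| Passing count | Alpha at 35% | Power at 50% |
|---|---|---|
| 42 or more | 5.6% | 92.3% |
| 43 or more | 3.6% | 88.9% |

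The side on which 42 falls therefore decides whether the 5% level holds.

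**5. Where the count fits.** Take the smallest count c with P(X ≥ c | n, 0.35) ≤ 0.05. It is 41 at n = 93, 42 at n = 94 to 96, 43 at n = 97 and 98, and 44 at n = 99. So 42, read as either at-least-42 or more-than-42, is right only for about 94 to 98 eligible.

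**6. Other denominators (assumed, because the number eligible is not in the document).**

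| Eligible | Amber counts | Passing count, exact 5% test | Grade under the 42 rule |
|---|---|---|---|
| 80 | 28–39 | 36 | all amber is major |
| 97 | 34–48 | 43 | 43–48 minor; 42 undefined; 34–41 major |
| 120 | 42–59 | 52 | 43–59 minor; 42 undefined |
| 140 | 49–69 | 59 | all amber is minor |

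*Small denominators.* At 80 eligible, results of 36 to 39 (45.0% to 48.8%) pass the test but are graded major. The minor grade disappears at 86 or fewer eligible, because 43/86 is already 50%, which is green.

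*Large denominators with 50 randomized.* The passing count first exceeds 50 at n = 117, where it is 51; at n = 142 it is 60. Over that range the rate runs from 50/117 = 42.7% to 50/142 = 35.2%, all amber. The count of 50 exceeds 42, so the grade is minor although the test is not passed. At n = 143, 50/143 = 34.97% and the result is red by rate.

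**7. The proposed rule at n = 97.** The exact one-sided 95% lower limit is 34.8% for 42 of 97 and 35.7% for 43 of 97. It therefore assigns 42 to major and 43 to minor.

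**The case against.** **The split applies only inside amber.** This stands, and it limits the point. A reader might infer that 41 of 70 (59%) would be graded as needing major changes. The sentence about results below 42 reads naturally as the second half of the amber sentence, and 59% is green by rate. A reader might also infer that a trial reaching 50 passes whatever its rate. It passes the count of 42, but from 143 eligible it is red under Table 1.

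**Large false-pass probabilities are not supported.** At a true rate of 35% and 130 eligible, the chance of exceeding 42 is 71%. But 43 to 45 of 130 are below 35% and hence red; the chance of 46 or more is 49.6%. Even that treats the number eligible as fixed and the number randomized as unlimited, while the design aims for 50. The conclusion does not rest on these figures.

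**The denominator may be close to 97.** The document does not settle this. Sample Size and Power attaches 97 to families approached, while Table 1 and the Recruitment section attach it to eligible parents. Consent comes before screening, so the eligible number could fall well below the number approached. Conversely, 130 to 140 eligible with 50 randomized would mean losing 80 to 90 consented, eligible families before randomization, which is doubtful. The small-denominator failure is at least as plausible as the large one.

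**The SAP may adapt the cut-off.** It may, and silence on that would be no finding. But the article states the rule, leaves a value unassigned and prints a wrong percentage; those are faults in the text as it stands.

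**The power shortfall is trivial.** Agreed. Under the literal more-than-42 reading, 88.9% against 90% is discreteness around a sound n = 97.

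**Conclusion.** The point holds in a limited form. The amber split is stated as a count that fits only about 94 to 98 eligible parents, although the rate's denominator is observed. Exactly 42 has no action, and 54% should be 43%. The two textual faults need no assumption. The misgrading does depend on a denominator away from 97: at 80 eligible, 36 to 39 randomized is graded too harshly; with 50 randomized and 117 to 142 eligible, the result is graded too leniently.

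The consequence is bounded. The green and red limits are unaffected, only the minor/major grade within amber is at issue, and the abstract says progression also draws on qualitative and economic findings. The sample size of 97 is not in question.

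**What to change.** Keep the green and red limits. Replace the two sentences on 42 with one: within amber, recruitment needs minor adjustments if the exact one-sided 95% lower confidence limit for the proportion of eligible parents randomized, at the observed number eligible, exceeds 35%, and major changes otherwise. For the planned 97 this is 43 or more against 42 or fewer. If the planned critical value is still shown, print it as 42 of 97 (43%).

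The cost is one sentence and one corrected percentage, with no new data. The Results section says recruitment is complete, so the number eligible should now be obtainable. The re-expressed cut-off must therefore be reported as a post hoc clarification, derived mechanically from the 35% limit and 5% level already stated. Optionally, note that at n = 97 the more-than-42 rule has exact alpha 3.6% and power 88.9%.

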##### Study Retention

This will be measured as the percentage of participants who have completed at least one questionnaire at the 6-month follow-up among all those who consented to participate. The criterion to be met is that at least 70% of randomized participants are retained at the 6-month follow-up (60%-69% falls within the amber zone and <60% within the red zone). See Table 2 for a full list of questionnaire measures.

**Table 2 table2:** Full list of data collection measures completed within the trial.

Measure	Screening	Baseline	3-Month follow-up	6-Month follow-up
VABS-3^a^ (socialization and communication subsections only at the 6-month follow-up)	✓			✓
PHQ-4^b^		✓	✓	✓
PSOC^c^		✓	✓	✓
CPRS^d^		✓	✓	✓
APQ^e^		✓	✓	✓
DBC-2^f^		✓		✓
CA-SUS^g^		✓		✓
ESQ^h^			✓	
GBO^i^ (VIG^j^ therapist only)			✓	
Process evaluation semistructured interview				✓

^a^VABS-3: Vineland Adaptive Behaviour Scale (Vineland–3) [54].

^b^PHQ-4: Patient Health Questionnaire-4 [55].

^c^PSOC: Parenting Sence of Competence Scale [56].

^d^CPRS: Child-Parent Relationship Scale [57].

^e^APQ: Alabama Parenting Questionnaire [58].

^f^DBC-2: Developmental Behaviour Checklist-2 [59]

^g^CA-SUS: Child and Adolescent Service Use Survey [60].

^h^ESQ: Experience of Service Questionnaire [61].

^i^GBO: Goal Based Outcomes [62].

^j^VIG: video interaction guidance.

##### VIG Completion

This will be measured by the number of participants in the intervention group who complete at least three VIG cycles. The criterion to be met is that at least 80% of participants receive 3 VIG cycles (65%-79% fall within the amber zone and <65% within the red zone). A VIG cycle is defined as 1 meeting to record a parent-child interaction and 1 meeting to view and discuss edited clips of the most attuned moments during the shared review.

#### Secondary Outcomes

##### Overview of Secondary Outcomes and Health Economic Evaluation

Secondary outcomes will include the completeness of outcome measures (ie, usable items), acceptability, barriers and facilitators to engaging with remote VIG for both parents and VIG practitioners, and the feasibility of remote implementation (both VIG and study processes). This will encompass aspects such as VIG fidelity, perceived effectiveness, potential adaptations, and any unintended implementation failures. The health economic evaluation will assess the feasibility of measuring health and social care services utilized by children with IDs whose parents participate in either the treatment as usual or VIG groups. This evaluation will include information on medications used by both the study participants and their children with IDs. Additionally, the health economics evaluation will aim to estimate the total cost of delivering remote VIG and assess how these costs compare with those of providing treatment as usual.

Qualitative data will be collected from semistructured interviews with participants, VIG practitioners, and service managers. These interviews will focus on discussions about participants’ experiences engaging with the research tasks, including what they found favorable or unfavorable about the research process and the intervention itself. Additionally, participants will be invited to share suggestions for potential improvements in both the research methodology and the delivery of the intervention.

Health economics data will be collected through telephone-based interviews with participants, conducted at baseline and at the 6-month follow-up, as well as through an online survey completed by clinical staff at the 3-month follow-up. Health and social care utilization will be captured via the telephone interview by adapting the Child and Adolescent Service Use Schedule (CA-SUS) for this study. This questionnaire has been previously adapted for this population [14] and includes items related to primary and secondary care services, as well as medications used over the past 6 months. Service use will be costed using unit costs from the Personal Social Services Research Unit, while medication costs will be determined using the British National Formulary. The CA-SUS will aim to collect all relevant health and social care utilization data, including any service use components that may overlap between VIG and TAU interventions. Costs associated with the delivery of VIG will be gathered through an online survey completed by staff. This survey will collect data on staff salary banding and the number of hours spent on delivery-related tasks.

The economic evaluation will be conducted from a health and social care perspective; therefore, recruitment costs will be excluded.

The secondary outcomes will be analyzed as described in the following sections.

##### Completeness of Outcome Measures

This will refer to the number of participants who provide usable data for each study measure, estimated separately at each time point. The definition of “usable” data will be based on having enough items to allow for the calculation of a total or subscale score. The percentage of participants who provided data on the DBC-2 [59] at the 6-month follow-up will be estimated among those recruited (likely the primary outcome in the final trial). A green signal for completeness will be defined as having 80%-100% usable data for DBC-2 scores. Any measure with less than 70% usable data will be reevaluated.

##### Acceptability of VIG

Qualitative data from interviews with parents, VIG practitioners, and service managers will be analyzed using framework analysis to assess the acceptability of VIG [63]. This analysis will also identify key barriers and facilitators to engaging with remote VIG.

